#### Secondary outcomes

Secondary outcome data will be obtained from routinely collected information through the count data (programme data) from records, registers and review documents on response rate only in the intervention villages. It will be complemented by qualitative data analysis.

#### Missing data

Participants in either study arm who have incomplete data/no data by the end of the study will be considered as missing data/lost to follow-up. No imputation will be made for participants with missing data. Subgroup analyses may be performed for participants with full versus partial intervention if appropriate. Similarly, we may perform sensitivity analysis to explore the impact of non-informative loss to follow-up by conducting a complete case analysis.

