### Measures

The primary outcome of the integrated suicide prevention programme is a reduction in suicides and attempted suicides in the intervention villages compared to control villages. In addition, each intervention has its own primary and secondary outcomes (Table 1).

**Table 1 Tab1:** Primary and secondary outcomes of specific interventions of the cluster-randomised controlled trial

Interventions	Primary outcome	Secondary outcomes
Intervention 1: suicide prevention in schools through the Youth Aware of Mental Health (YAM) intervention	Reduction in suicidal ideation at 3-month and 12-month follow-up among adolescents in intervention schools	▪ Proportion of schools that agreed to implement the YAM intervention of the total number of schools approached for implementation ▪ Of those schools that agreed to implement the YAM intervention, the proportion of schools that implemented the programme ▪ Proportion of adolescents in intervention schools who received the YAM programme out of total number of adolescents in the selected grade
Intervention 2: community storage facilities (CSF) for pesticides	Reduction in the number of suicides and attempted suicides in intervention villages at 12-month follow-up	▪ Proportion of villages of those that were approached that agreed to have the CSF ▪ Proportion of villages that agreed to have the CSF or provided for or arranged space to build the storage facility ▪ Proportion of households reached with promotion activities linked to community storage of pesticides; proportion of households that requested a community storage box; proportion of households that received a community storage box ▪ Proportion of households in the villages that used the boxes regularly
Intervention 3: community health worker (CHW) training for identification, support and management of people at risk of suicide or self-harm	Number of persons with suicidal ideation detected by trained CHWs and number of persons referred by CHWs to mental health professionals for care for suicidal ideation	▪ Proportion of health workers trained in intervention villages ▪ Improvement in knowledge, skills, attitudes and practice of CHW who received training ▪ Number of CHWs applying knowledge and skills obtained through the training programme in their day-to-day practice at 6-month and 12-month follow-up

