#### Intervention 1: YAM in schools: primary outcome

Suicidal ideation among young adolescents in both intervention and control condition schools will be assessed using the Suicidal Ideation Attributes Scale (SIDAS) [32]. SIDAS is a 5-item self-report scale addressing attributes of suicidal thoughts: frequency, controllability, closeness to attempt, level of distress associated with thoughts and impact on daily functioning. Scores ≥ 21 indicate a high risk of suicidal behaviour among youths. In this study, the SIDAS score will be assessed at baseline and at 3-month and 12-month follow-up. If a student has elevated scores on suicidal ideation (≥ 21 out of a maximum score of 50) at baseline assessment, he/she will be referred to the closest locally available health services such as a primary care centre, district mental health hospital or the Hospital for Mental Health in Ahmadabad (tertiary specialised mental health hospital).

Depression symptoms will be assessed using the Patient Health Questionnaire-9 (PHQ-9), a 9-item self-report scale [33, 34]. The PHQ-9 will be administered to students in the intervention and control schools at baseline and 3-month and 12-month follow-up. PHQ-9 scores range from 0 to 27 with higher scores indicating greater symptom severity. Scores of 5, 10, 15 and 20 represent cut-offs for mild, moderate, moderately severe and severe depression, respectively. Students who meet criteria for severe depression (scores > 20 on the PHQ-9 scale) at baseline assessment will be referred to the closest locally available health services such as a primary health centre, district mental health hospital or the Hospital for Mental Health in Ahmedabad (tertiary specialised mental health hospital).

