### Data analysis and reporting

All findings from the trial will be reported in accordance with SPIRIT, Extended CONSORT and CHEERS guidelines. For analysis of quantitative data, we will first tabulate descriptive statistics for all study variables to understand trends in the data. For efficacy analysis of the primary outcome, we will apply an intention-to-treat (ITT) approach to all participants assigned to the intervention arm as randomised, regardless of the study intervention received. We will test the null hypothesis of no difference in the population incidence of suicides and attempted suicides between clusters allocated to the intervention and control arms, using surveillance data.

A multilevel Poisson regression model will be employed, with inflated standard error to accommodate the clustered design. Inflation will be achieved using a normal or gamma distributed random effect, whichever best describes the variation in number of suicides across villages. Change in suicide and attempted suicide rates from baseline to follow-up (12 months) at intervention and control sites will be calculated separately, adjusting for random cluster effect. We will compare this change in the intervention and control arms and calculate the 95% confidence interval.

If there is statistical evidence of over-dispersion in the Poisson regression model, a negative binomial regression analysis will be performed. Allowance will be made if a greater than expected number of clusters without a case of suicide/suicide attempt is observed, using the Stata zero-inflated negative binomial regression (“zinb”) command or zero truncated Poisson regression for instance, which includes a test of whether this approach offers an improvement over the standard model. All hypothesis testing will be carried out at the 5% (two-sided) significance level. *P* values will be rounded to 2 decimal places. *P* values below 0.05 will be reported as < 0.05 in tables.

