#### Specific analysis for each intervention

For intervention 1, differences in PHQ-9 and SIDAS scores at 12-month follow-up between students in the intervention and control arms will be calculated using a multilevel, linear effect model adjusting for clustering by villages as a random effect. We will analyse the SIDAS scores both on a continuous and categorical scale. Parameters for categorical variables will be either no ideation versus ideation or tertile scores (low/medium/high).

For intervention 2, all the secondary outcome data as per Table 1 will be analysed and presented as summary tables using count data and logs maintained by research team. Additionally, data from survey responses from a structured questionnaire from four villages (two control, two intervention) will be analysed pre and post intervention to evaluate pesticide purchase, storage options and acceptability and use of the CSF in the intervention villages.

For intervention 3, due to the ordinal nature of the data (knowledge, skills and attitude scales), multilevel ordered logistic regression (ordinal logistic regression) will be employed to assess change in knowledge, skills and attitude from baseline to follow-up in both intervention and control groups. Adjusted and unadjusted estimates will be reported as the proportional odds ratio or log odds coefficient. The number of persons with suicidal ideation detected and referred on by trained CHWs will be recorded as count data through logs and daily record registers. All the count data will be analysed using descriptive statistics.

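### The missing-data rule treats partly observed participants as lost, and the 12-month-only model leaves 3-month SIDAS scores unused although Table 1 makes them primary

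*Protocol article*

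**What the plan says.** All references are to the protocol article.

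- **Missing data.** Participants in either arm "who have incomplete data/no data by the end of the study will be considered as missing data/lost to follow-up". The next sentence reads "No imputation will be made for participants with missing data". The section closes with an option: "we may perform sensitivity analysis to explore the impact of non-informative loss to follow-up by conducting a complete case analysis". It does not define incomplete by item, scale or visit.
- **Measures, Table 1.** The primary outcome for intervention 1 is "Reduction in suicidal ideation at 3-month and 12-month follow-up among adolescents in intervention schools".
- **Intervention 1: YAM in schools: primary outcome.** "the SIDAS score will be assessed at baseline and at 3-month and 12-month follow-up"; the PHQ-9 follows the same schedule.
- **Specific analysis for each intervention.** The model for intervention 1 addresses "differences in PHQ-9 and SIDAS scores at 12-month follow-up between students in the intervention and control arms", with village as a random effect. No model is given for month 3.
- **Intervention 3: primary outcome.** Health workers' knowledge, attitudes, skills and practice (KAP) are assessed at 6 and 12 months in both arms.
- **Sample size for intervention 1.** 2866 students, multiplied by a design effect of 1.59 to give 4557. No allowance for attrition is stated.
- **Data collection.** Absent participants get up to three further visits, so missed assessments are expected.

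**The concern.** Missingness is a property of an outcome at a visit. The rule assigns it to the participant and gives someone with some data the same label as someone with none. A student seen at baseline and 3 months but absent at 12 months has a 3-month SIDAS score that Table 1 calls primary, yet is classed as lost. A student absent only at 3 months is incomplete too, although the stated model needs only the 12-month score. The same applies to a health worker with a KAP assessment at 6 or 12 months but not both.

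The analysis section adds to the problem. Its model for SIDAS and PHQ-9 takes only the 12-month score, so an observed 3-month score contributes nothing even for a student with complete data. Half of the stated primary outcome for intervention 1 has no model, and the information that a 3-month score carries about a missing 12-month score is not used.

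Precision on the student and health-worker outcomes is at stake. There is also an exposure to bias if those who miss a visit differ from those who do not. The student sample size leaves no margin for either.

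**Working it through.** **1. The Missing data section against itself.** There are two ways to read it.
- *Incomplete participants leave the analysis.* With no imputation, the main analysis is then already a complete-case analysis, and the proposed sensitivity analysis is the same analysis again.
- *Incomplete participants stay in with the scores they have.* The complete-case analysis is then a real alternative, but the sentence classing these participants as missing or lost is wrong.

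The text needs changing on either reading.

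**2. The plan's own sample size.** Inputs from the sample size section for intervention 1: 19% against 15%, two-sided alpha 0.05, power 80%.
- Pooled-variance formula: n = [1.960·√(2·0.17·0.83) + 0.842·√(0.19·0.81 + 0.15·0.85)]² / 0.04² = 1383.2 per arm.
- With continuity correction: (1383.2/4)·[1 + √(1 + 4/(1383.2·0.04))]² = 1432.7, so 1433 per arm and 2866 in total. This matches the plan.
- 2866 × 1.59 = 4556.9, so 4557. This matches too, and no further inflation follows.

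**3. Power as students are lost.** The document gives no loss rate for students, so the rates below are assumptions. Effective n per arm = 2278·(1 − loss)/DE. Power = Φ{[0.04·√n − 1.960·√(2·0.17·0.83)] / √(0.19·0.81 + 0.15·0.85)}, without continuity correction. Two versions of the design effect (DE) are shown:
- DE fixed at 1.59.
- DE shrinking with cluster size, assuming 124 equal clusters: 4557/124 = 36.75 students each, implied ICC 0.59/35.75 = 0.0165, DE = 1 + (36.75·(1 − loss) − 1)·0.0165.

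| Loss | Power, DE fixed | Power, DE shrinking |
|---|---|---|
| 0% | 81.4% | 81.4% |
| 10% | 77.2% | 78.8% |
| 19% | 72.8% | 75.9% |
| 20% | 72.2% | 75.6% |
| 36% | 62.6% | 69.0% |

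**4. How much of the loss comes from the rule.** Let v be the share missing each follow-up, independently. If only the 12-month score is needed, the loss is v. If missing either follow-up excludes the student, it is 1 − (1 − v)².
- v = 5%: 9.8% instead of 5%.
- v = 10%: 1 − 0.9² = 19% instead of 10%. Power is 72.8–75.9% instead of 77.2–78.8%.
- v = 20%: 1 − 0.8² = 36% instead of 20%. Power is 62.6–69.0% instead of 72.2–75.6%.

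Independence matters. If the same students miss both visits, the rule adds no loss beyond v. The figures are for the two-proportion comparison used to size the study, not for the linear model of the scores.

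**The case against.** The best defence is that the text never says that observed scores are removed. It labels participants, declines to impute, and names complete-case analysis only as a sensitivity analysis, which suggests a main analysis that keeps more. This is fair, and exclusion is therefore a literal reading rather than an explicit statement. It does not rescue the section, because no other handling is described and the label is then wrong.

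A second objection is that 3-month scores go unused because of the 12-month model, not because of the missing-data rule. That is correct, and so both places need changing. The three visits to absentees and the completeness checks on forms will also limit losses, though they cannot remove them.

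A reader might go further in three ways that the document does not support.
- *One blank item voids a whole SIDAS, PHQ-9 or KAP score.* No item threshold is stated, and scoring a scale with a blank item is commonly left to the analysis plan or the instrument's rules.
- *Students without ideation leave the later SIDAS items blank, so analysed prevalence is inflated and the arm contrast biased.* The article says only that "SIDAS is a 5-item self-report scale addressing attributes of suicidal thoughts: frequency, controllability, closeness to attempt" and two further attributes are covered. It gives no response options, skip pattern or zero-scoring rule. Any blank rates by arm would be invented, and with them the bias.
- *Student attrition will be 20%.* That figure belongs to the sample size for intervention 2. The 20% in the table above is only an illustration.

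**Conclusion.** The point holds for participants and visits. The rule puts partial and absent data in one class. Taken literally, it treats as lost a student or health worker who has observed outcome scores, and it makes the named sensitivity analysis redundant. Separately, the stated model leaves the 3-month part of the intervention 1 primary outcome unused.

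The size cannot be derived from the document. With assumed losses, power for intervention 1 goes from about 81% at no loss to about 72–76% at 20% loss. With independent misses of 10% per visit, the literal rule nearly doubles the excluded share, from 10% to 19%.

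One might infer that the trial's main result is at risk. It is not: the programme's primary outcome is a count of suicides and attempts from village surveillance, and these questionnaires do not enter it. The point merits a correction because it concerns a component's primary outcome, and the correction is cheap.

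**What to change.** 1. In Missing data, replace the classification rule with: *Missingness is judged separately for each outcome and visit; every observed score is analysed.* This covers SIDAS, PHQ-9 and KAP.
2. In the analysis for intervention 1, fit SIDAS and PHQ-9 at 3 and 12 months in one mixed model with village and student random effects and visit-specific arm effects. Students seen at only one follow-up then contribute, and both time points in Table 1 are estimated.
3. Drop the complete-case analysis as a sensitivity analysis wherever it equals the main analysis.
4. Leave item-level scoring and any pro-rating to the analysis plan and the instruments' scoring rules.

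The cost is a few lines of wording and slightly more programming; no new data are needed. The mixed model relies on a missing-at-random assumption, which should be stated.

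### For the student and health-worker scales, the only missing-data sensitivity analysis is an optional complete-case analysis, which cannot show the effect of informative loss to follow-up

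*Protocol article*

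**What the plan says.** The protocol article's Missing data section makes these statements:

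- Who counts as missing: "Participants in either study arm who have incomplete data/no data by the end of the study will be considered as missing data/lost to follow-up".
- How they are handled: "No imputation will be made for participants with missing data".
- An exposure analysis: "Subgroup analyses may be performed for participants with full versus partial intervention if appropriate". This concerns how much of the intervention was received, not missing outcomes.
- The one missing-data sensitivity analysis: "we may perform sensitivity analysis to explore the impact of non-informative loss to follow-up by conducting a complete case analysis".

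Under Specific analysis for each intervention, the intervention 1 analysis estimates "differences in PHQ-9 and SIDAS scores at 12-month follow-up between students in the intervention and control arms", using a multilevel linear model with village as a random effect. SIDAS is analysed on both a continuous and a categorical scale. For intervention 3, "multilevel ordered logistic regression (ordinal logistic regression) will be employed to assess change in knowledge, skills and attitude from baseline to follow-up".

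The Measures sections schedule SIDAS and PHQ-9 at baseline, 3 months and 12 months. They schedule KAP at 6 and 12 months in both arms. Table 1 makes suicidal ideation at 3 and 12 months the primary outcome of intervention 1.

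**The concern.** A missing-data sensitivity analysis should relax the assumption on which the main analysis rests. Here the main analysis imputes nothing, so a comparison of 12-month scores already rests on students who have one. A complete-case analysis makes the same kind of restriction and relaxes nothing.

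The stated target is also the wrong one. Loss unrelated to the outcome costs precision but does not bias the comparison of those who remain. Loss related to the outcome can bias it, and the section names no analysis for that case.

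Suicidal ideation is the primary outcome of intervention 1, and absence from a school assessment could plausibly be related to it. If that relation differs between arms, part of an apparent benefit, or of an apparent lack of one, could come from who was seen at 12 months. Agreement between the main and complete-case results would say nothing about this.

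**Working it through.** **1. The planned effect.** The intervention 1 sample size section gives 19% v 15%, 80% power and two-sided alpha of 0.05. The continuity-corrected two-proportion formula gives 1,433 per arm, or 2,866 in total, as stated. Then 2,866 × 1.59 = 4,556.9, which rounds to the stated 4,557. The planned difference is 19 − 15 = 4.0 points (3.8 points if the 20% relative reduction is taken literally, since 0.20 × 19 = 3.8). No attrition allowance appears in this calculation. The 20% in the protocol belongs to the intervention 2 population figure.

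**2. Main analysis against the sensitivity analysis.**

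- *SIDAS and PHQ-9.* With no imputation and a 12-month comparison, a student without a 12-month score contributes nothing to it. A complete-case analysis drops the same student. If complete-case means complete at every wave, it also drops students who have a 12-month score but missed another wave. That changes the sample a little but still assumes that those dropped are like those kept.
- *KAP scales.* The model is for change from baseline to follow-up, and a multilevel fit to all available records can differ somewhat from a strict complete-case fit. Neither fit varies the outcome of the people who were lost.

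**3. Size of the bias that would go unseen.** Let d be the share lost and g the prevalence among the lost minus the prevalence among the retained. True prevalence in an arm is (1 − d) × retained + d × (retained + g) = retained + d × g, so the observed figure is too low by d × g. The bias in the between-arm difference is d × g in the intervention arm minus d × g in the control arm.

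Assumptions: g = 10 points in the intervention arm, 0 in controls, and d from 10% to 30%.

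| Loss | Bias (points) | Share of 4.0 points |
|---|---|---|
| 10% | 0.10 × 10 = 1.0 | 25% |
| 20% | 0.20 × 10 = 2.0 | 50% |
| 30% | 0.30 × 10 = 3.0 | 75% |

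With the same loss and gap in both arms the bias is zero, for example 2.0 − 2.0 = 0 at 20% loss.

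**4. Is a 10-point gap extreme?** Suppose true prevalence is 19% in both arms, 20% are lost in each, and intervention students with ideation are lost at 1.5 times the rate of others. The rate for others is 0.20 / (0.19 × 1.5 + 0.81) = 0.1826, and for those with ideation 0.2740. Observed prevalence is 0.19 × (1 − 0.2740) / 0.80 = 17.2%. Prevalence among the lost is 0.19 × 0.2740 / 0.20 = 26.0%. The gap is 8.8 points and the spurious benefit 1.8 points. At twice the rate the spurious benefit is 3.2 points. A 10-point gap therefore corresponds to selective loss between 1.5 and 2 times, in one arm only.

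**5. What a tipping-point analysis would report.** Suppose 15% v 19% is observed and lost controls are at 19%. The difference disappears when prevalence among lost intervention students is (0.19 − (1 − d) × 0.15) / d. This gives 55% at 10% loss, 35% at 20% and 28% at 30%. A reader can judge whether such values are credible; a complete-case analysis offers nothing comparable.

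**The case against.** The strongest reply is that this is a condensed article. Delta-adjusted and tipping-point methods are commonly left to the statistical analysis plan, which is not shown, so their absence here is no fault. That is right, and it rules out inferring that informative loss will never be examined in this trial. What remains is a method that the article does state, and aims at loss that does not bias the comparison.

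Three other strong readings are not supported:

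- *That the sensitivity analysis must return exactly the main result.* The article does not say whether baseline or 3-month scores enter the intervention 1 model, nor whether complete-case means complete at all waves. For KAP the two fits can differ. Essentially the same students is as far as the text goes, and only for SIDAS and PHQ-9.
- *That the plan would certify robustness.* The analysis is only something the team may do, and no robustness claim is attached to it. Equally, even this check is not committed to.
- *That the trial's main result is at risk.* The programme primary outcome is a village-level count from key informants, health facilities and police records. Student and health-worker loss does not enter it.

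The protocol also plans three follow-up visits for absent participants (Data collection). That should reduce loss but does not address whatever loss remains. The choice between a repeated-measures model and multiple imputation is partly preference, since either would be acceptable.

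**Conclusion.** The point holds for the individual-level outcomes: SIDAS and PHQ-9 in students, and KAP in community health workers. The stated sensitivity analysis is optional, adds little or nothing to the no-imputation analysis of 12-month student scores, and examines informative loss in neither setting.

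The illustrated bias of 1.0 to 3.0 points, a quarter to three quarters of the planned 4-point difference, depends on assumptions that the protocol does not supply: loss of 10% to 30%, a 10-point gap among lost intervention students, and no gap among lost controls. It is not a prediction. The bias shrinks as the arms become alike and reverses if the gap is larger among controls. The illustration concerns ideation prevalence, so it bears most directly on the categorical SIDAS analysis and the sample size. The point deserves correction because it touches the primary outcome of intervention 1.

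**What to change.** 1. **Main analysis of SIDAS and PHQ-9.** Fit one mixed model to the baseline, 3-month and 12-month scores of all students with any follow-up, with effects for student and village, and report the 12-month contrast. This is valid if data are missing at random given the observed scores, and it keeps students who were seen at 3 months but not at 12. Use the corresponding mixed model for categorical SIDAS. Multiple imputation within arm that respects the clusters is an acceptable alternative, but would require changing the no-imputation sentence.
2. **KAP.** Do likewise with the 6- and 12-month data in the ordered logistic model.
3. **Sensitivity analysis.** Replace the complete-case sentence with a commitment to a delta-adjusted (tipping-point) analysis. It should vary the outcome among lost participants separately by arm over a range stated in advance, and report where the conclusion changes.
4. **Scope.** State that this section applies to the individual-level scales and not to the surveillance outcome.

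The cost is revised wording and modest extra programming. No new data are needed, because every wave used is already scheduled.
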